### Experimental approach

We will compare the effects of CONC, ECC and the combination of CONC + ECC training on the changes in exercise performance (aerobic capacity and muscle strength), muscle mass, functional performance, levels of physical activity, quality of life, changes in biomarkers of cardiometabolic health (insulin resistance and lipid profile) and systemic inflammation. The proposed study is a multicentre randomised trial that will employ a 3 (groups) × 2 (measure times: Pre- and Post-) repeated measures design. The total duration of the proposed study is 14 weeks, including a 12-week training period and a testing week before and after the intervention. A stratified randomised assignment upon sequential number (by block) process will ensure that the experimental groups are balanced for FEV_1_, sex, and age. The allocation sequence will be performed by the multicentre coordinator. The training sessions will be conducted at three clinical centres in Santiago, Chile (Instituto Nacional del Torax, Hospital Clinico Universidad de Chile, Hospital Clinico Universidad Catolica). Assessors of all outcomes will be blinded to the group allocation of participants, which will not be revealed during the participation of the study.

### Participants

Sixty-six participants diagnosed with severe COPD (FEV_1_ < 50% of predicted; quartiles 3 and 4 in the BODE [Body-mass index, airflow Obstruction, Dyspnoea, and Exercise] index) will be recruited via newspaper advertisements, posters, flyers, visits to local community centres and referral from associated centres. The sample size calculation revealed that based on an α level of 0.05 and a power (1-β) of 0.8, and effect sizes ranging from 0.6 to 1.2 found in similar outcomes (muscle CSA, 6MWT) in our preliminary data after eccentric training, and few studies using combined eccentric and concentric cycling [67–69], a minimum of 17 patients would be necessary per group for this study. However, 22 patients per group will be recruited to account for a typical dropout rate of 30% in long-term training studies. Accredited Ethics Committees from all three Hospitals and universities have approved this study. Any important modification will be informed to the ethics committees. All participants will obtain medical permission from a pulmonary medical specialist before taking part in the study. Exclusion criteria will be: current insulin therapy, long-term oxygen therapy, asthma, other concomitant pulmonary diseases, or other diseases that could affect physical activity [70, 71]. Participants will be instructed to continue with normal everyday activities yet be dis-encouraged from engaging in any unaccustomed training or supplementary nutrition and will be fully informed of the nature and possible risks of all of the experimental procedures before providing their written informed consent. Written informed consent will be obtained from the multicentre coordinator. Criteria for discontinuing intervention will be upon participant request or worsening disease. Patients will receive an initial report for all their clinical assessments, which will be upgraded at the end of the study participation. Participants will be coded as sequential number upon recruitment. A Data Monitoring Committee (DMC) will not be necessary as it will be a short intervention and with sample size that can be handle by the research team. Adverse events will be collected and reported appropriately. All personal information will be coded, and data collected will be kept confidential, and only the PI and multicentre coordinator of this study will have access to the files. The computer will be held in the PI office.

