### Molecular analyses

A subgroup of participants will undertake muscle biopsies (n = 30). This sample size was estimated using data from previous studies [79] in which muscle fibre type [26, 28], MRF (i.e., myostatin, MyoD) [26, 32], and phosphorylation of p70S6K [32, 80] increased after training interventions (i.e., aerobic and resistance training). Thus, based on effect sizes ranging from 1 to 2.5 from those studies and an α level of 0.05 and a power (1-β) of 0.8, it was found that eight patients per group would be sufficient. To account for a possible 30% dropout, we will recruit ten patients per group in this study. Muscle biopsies will not be performed on individuals on anti-platelet or anti-coagulation therapy [81].

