### Statistical analysis

The primary analysis will follow an intent-to-treat approach. A two-way analysis of variance (ANOVA) will be used to compare the three intervention groups and time (Pre- and Post-). If an interaction effect is found, a Tuckey´s post hoc test will be used for pairwise comparisons. Differences will be considered statistically significant at the 0.05 level (two-sided).

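### The 30% dropout allowance is calculated as n × 1.3 instead of n / 0.7, so 22 and 10 recruits per group leave about 15 and 7 completers, short of the 17 and 8 the plan asks for

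*Protocol article*

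**What the plan says.** In the protocol article, Methods, Participants, the sample size for the main study is "based on an α level of 0.05 and a power (1-β) of 0.8, and effect sizes ranging from 0.6 to 1.2", and it concludes that "a minimum of 17 patients would be necessary per group for this study". The recruitment target follows: "22 patients per group will be recruited to account for a typical dropout rate of 30% in long-term training studies". The section opens with the total, "Sixty-six participants diagnosed with severe COPD", which is 3 × 22.

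Molecular analyses repeats the pattern for the biopsy subgroup. At the same alpha and power, "it was found that eight patients per group would be sufficient". Then: "To account for a possible 30% dropout, we will recruit ten patients per group in this study". The total is given as 30, which is 3 × 10.

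Neither section shows the inflation formula, and neither mentions any other reserve, such as replacement of dropouts.

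**The concern.** Each section gives three numbers: the patients needed, the expected loss and the patients recruited. Any two of them fix the third, and in both sections the three disagree. A dropout rate is a fraction of those who enter, so the number to recruit is the number needed divided by one minus the rate. Adding 30% of the number needed gives a smaller figure, and the gap widens as the rate rises.

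At stake is the statement that the trial keeps its planned information after the loss it expects. As written, readers and ethics committees are told that a 30% loss is covered when it is not, in both the clinical and the molecular study.

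**Working it through.** **Inputs.** From Participants: 17 needed per group, 22 recruited, 30% dropout, three groups, alpha 0.05, power 0.80. From Molecular analyses: 8 needed, 10 recruited, 30% dropout, three groups. From Statistical analysis: two-sided testing.

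**Reproducing the plan's figures.** Multiply the requirement by (1 + dropout) and round down:
- Main study: 17 × 1.3 = 22.1, giving 22.
- Biopsy subgroup: 8 × 1.3 = 10.4, giving 10.

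Both published figures come out exactly. The same pattern in two separate sections suggests a method error, not a misprint.

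**Expected completers = recruits × (1 − dropout).**
- Main study: 22 × 0.70 = 15.4, against 17 needed.
- Biopsy subgroup: 10 × 0.70 = 7.0, against 8 needed.

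**Recruits needed = n / (1 − dropout), rounded up.**
- Main study: 17 / 0.70 = 24.3, so 25 per group and 75 in total, against 66.
- Biopsy subgroup: 8 / 0.70 = 11.4, so 12 per group and 36 in total, against 30.

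**Dropout the planned sizes can absorb = 1 − needed / recruited.**
- Main study: 1 − 17/22 = 22.7% (five losses per group).
- Biopsy subgroup: 1 − 8/10 = 20% (two losses per group).

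**Chance of keeping the required number.** Assume that each patient drops out independently with probability 0.30. A group of 22 then keeps at least 17 with probability 0.313, and a group of 10 keeps at least 8 with probability 0.383. For the correctly inflated sizes the corresponding chances are 0.677 (at least 17 of 25) and 0.724 (at least 8 of 12).

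**Effect on power.** The article gives ranges of effect size and does not name the test behind 17 or 8, so this step is illustrative. I assume a two-sample, two-sided t-test at 0.05 and solve for the standardised difference d that gives 80% power at the stated requirement.

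| | Needed | d for 80% power | Completers at 30% dropout | Power at that d | d detectable with 80% power |
|---|---|---|---|---|---|
| Main study | 17 | 0.99 | 15 | 74.5% | 1.06 |
| Biopsy subgroup | 8 | 1.51 | 7 | 73.5% | 1.63 |

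At the round value d = 1.0, which also leads to 17 per group, power is 80.7% with 17 and 75.3% with 15.

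**The case against.** The strongest reply is that the consequence is small and depends on an effect size the article never fixes. That is largely fair. Across the stated range of 0.6 to 1.2 for the main study, the same t-test with 15 per group has about 35% power at d = 0.6 and 89% at d = 1.2. With the full 17 per group these become 40% and 92%. The choice of d therefore matters much more than the inflation formula, and a loss of power from 80% to about 75% applies only at the d that makes 17 just enough. The planned analysis is also a group-by-time ANOVA with Tukey comparisons, so the t-test figures indicate scale and are not the trial's own power. None of this touches the contradiction, which uses only 17, 22, 8, 10 and 30%.

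A second reply is that the intent-to-treat analysis keeps all randomised patients. Some who stop training might indeed return for the final tests. But the design has one measurement before and one after training, so a patient without the second contributes no observed change. The article's own allowance also treats dropout as lost information.

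Third, the biopsy section calls eight sufficient, not a minimum, and describes 30% dropout as possible. The wording is softer and the expected shortfall is one patient per group. Even so, the section says that ten were chosen to cover that rate, and ten do not.

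Finally, the chance of keeping the full number is a demanding yardstick, since even 25 recruits meet it only about two times in three. The comparison of expected completers with the stated requirement is the better basis.

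**Conclusion.** The point holds. On the article's own figures, 22 recruits per group yield 15.4 completers where 17 are required, and 10 yield 7.0 where 8 are required. The planned sizes cover dropout of at most 22.7% and 20%, not 30%. Full cover of 30% would need 75 and 36 patients in total, against 66 and 30. This conclusion assumes only that a dropout provides no post-training measurement.

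The cost in power is modest, about 5 to 7 percentage points below the stated 80%. That size rests on a two-sided t-test and on the effect size for which 17 (or 8) per group gives exactly 80% power. The article names neither.

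**What to change.** Correct the statement in both sections, Participants and Molecular analyses, at the sizes already planned. Either of two forms will do:

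1. Say that at 30% dropout, 22 recruits per group are expected to give about 15 completers and 10 to give 7. Then give the resulting power or detectable difference, naming the effect size and test used.
2. Keep the requirements of 17 and 8, and say that the planned sizes maintain them up to 22.7% dropout in the main study and 20% in the biopsy subgroup.

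If the sizes are ever revised, inflate by n / (1 − dropout) and round up.

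The cost is wording in two paragraphs and a slightly less favourable power statement. No additional patients, and no change to the randomisation or analysis, are needed to make the text correct.

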### Characterisation and anthropometric measures of participants

Body mass and height will be determined with a scale and wall-mounted stadiometer (SECA, Germany). The subject´s age, body mass index (BMI), years of diagnosis, smoking habits, comorbidities, and medications will be recorded.

#### Lung function and pulmonary capacity

A spirometry test will be performed to assess the forced vital capacity (FVC) and FEV_1_ from which the FEV_1_/FVC ratio will be derived before and after bronchodilator administration. These measures will be assessed using a digital spirometer (TrueFlow, Switzerland) by a trained certified physiotherapist. The test will be repeated three times, and the best performance will be used for analyses [71].

#### Basal dyspnoea

The magnitude of dyspnoea will be assessed using the Medical Research Council dyspnoea scale; a scale of 5 points where 0 is not dyspnoea and 4 is the perception of patients feeling too breathless to leave the house [72].

#### 6-min walking distance test

The test will be conducted in a level enclosed 20 m corridor. Each participant will be instructed to cover as much ground as possible in six minutes. The test will be performed as recommended [73]. In addition, dyspnoea rates will be assessed at the end of the test.

#### BODE index

The BODE index will be calculated to characterise the patients, and it incorporates BMI, FEV_1_% predicted, score on the modified Medical Research Council dyspnoea scale, and 6-min walk distance to categorise the patients including a more integrated symptomatology method.

### Training protocols

Training will be performed three times per week on each other day, increasing intensity and time progressively over the 12 weeks. Each venue count with automated external defibrillators, oxygen supply, and instructed medical professionals in case of emergency.

*CONC:* The concentric cycling training will consist of 40 min cycling on a calibrated cycle ergometer (Life Fitness, USA). Time will start from 15 min and increase to achieve 40 min in week 4. The workload corresponding to 70% of VO_peak_ achieved during the incremental cycling test will be selected as the target intensity, and it will be monitored and adjusted by the rated perceived exertion (RPE; 6–20 scale), aiming for a target RPE of 14 (“somewhat hard”).

ECC: The eccentric cycling training will consist of 40 min cycling on an eccentric ergometer (Grucox, South Africa). Time will start from 15 min and increase to 40 min in week 4. The intensity will gradually increase to aim for an RPE = 14 “somewhat hard”. As the participant reaches the “somewhat hard” intensity, it will be maintained until the end of the training period, but power output per training session will increase as training progresses (as shown in previous studies) [35, 36].

*CONC* + *ECC:* This group will aim to perform 20 min of concentric cycling as in CONC and 20 min of eccentric cycling as in ECC in this order.

#### Training monitoring

Dyspnoea rates (1–10 scale), heart rate, and power output will be monitored during all training. Arterial oxygen saturation will also be constantly monitored and will be maintained in the 90% range at the lowest following clinical guidelines recommendations.

### Clinical outcomes

#### Blood samples

Resting venous blood samples will be collected following 12-h overnight fast from the antecubital vein will be collected in two EDTA and two serum vacutainer tubes and will be centrifuged for 10 min at 5000 rpm. Glucose and insulin concentrations, lipid profile (triacylglycerols, total cholesterol, high-density lipoprotein cholesterol, low-density lipoprotein cholesterol) and C-reactive protein will be assessed. Furthermore, inflammatory markers (IL-6, IL-1β, and TNF-α) and plasma microRNAs will also be analysed.

#### Functional performance

The timed up-and-go test will be performed to assess functional performance in addition to the 6MWT explained above. In brief, patients will be given verbal instructions to stand up from a chair, walk three meters as quickly and as safely as possible, turn around, walk back, and sit down. The test will be repeated three times, and the best performance will be used for analyses [74].

#### Quality of life and general wellbeing

The Spanish version of the St. George´s Respiratory Questionnaire for COPD patients (SGRQ-C) will be used to measure the participant’s functional health and well-being as in previous studies [75, 76]. It contains 50 items divided into three subscales (i.e., symptoms, activity, and impact), covering a wide range of aspects related with social functioning and psychological disturbances resulting from airways disease.

#### Cross-sectional area (CSA)

Magnetic resonance imaging (MRI) will be performed on both thighs after 15 min lay down rest. MRI images of both thighs will be T1 weighted. Images at 20%, 50%, and 80% distance from the patella and the anterior inferior iliac spine will be used for comparisons of the CSA of different portions of the quadriceps muscle. Whole quadriceps muscle CSA will be measured (ImageJ 1.41, NIH) [67].

#### Maximal voluntary isometric contractions (MVC) strength

Patients will be asked to perform three 3-s MVC of the dominant leg knee extensor muscle at 90° of knee extension; greater force out of three attempts will be used for analyses.

#### Maximal aerobic capacity

The peak oxygen consumption (VO_2peak_) and maximal concentric power output (PO_max_) will be determined during an incremental cycling test to exhaustion using a recumbent cycle ergometer (Livestrong, LS 5.0R model, USA) following the recommendation for COPD [77], using a breath-by-breath metabolic cart (Medisoft, Belgium).

#### Physical activity and sedentary behaviour

Habitual activity level will be assessed using a small, lightweight tri-axial accelerometer (Axivity, Ltd.) worn on the wrist for 24 h/day over seven days to determine the quantity and quality of movement and activity, e.g., activity counts and intensity, step count, sedentary time, number and duration of walking and sitting bouts. This measure will be taken during the first and last week of training [78].

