### Implication for practice

Muscle cross-sectional area, muscle function, functional performance, aerobic capacity, daily physical activity, and quality of life will be assessed before and after training. Muscle biopsies of vastus lateralis will be performed before and after training in severe COPD patients, from which muscle protein synthesis and degradation pathways will be analysed in a fibre specific manner.

The results from this study will provide important knowledge regarding the treatment of patients with COPD who are unable or non-compliant with conventional offered COPD rehabilitation settings as concentric cycling (i.e., endurance training) is the most provided exercise intervention for these patients. The study will also contribute to the existing knowledge regarding molecular mechanisms involved in the regulation of muscle mass in these patients.

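### Habitual physical activity is measured in the first and last training weeks, so it has no pre-training baseline and its change includes prescribed session time that rises by protocol

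*Protocol article*

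**What the plan says.** The section on physical activity and sedentary behaviour names the construct: "Habitual activity level will be assessed using a small, lightweight tri-axial accelerometer". The device is "worn on the wrist for 24 h/day over seven days", and the timing is fixed: "This measure will be taken during the first and last week of training".

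Other sections describe different timing:

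- Experimental approach sets a "3 (groups) × 2 (measure times: Pre- and Post-) repeated measures design" and a schedule "including a 12-week training period and a testing week before and after the intervention".
- Implication for practice lists the outcomes and says "daily physical activity, and quality of life will be assessed before and after training".
- Statistical analysis compares the groups over the two times, Pre and Post, and names no exception for accelerometry.

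Training protocols prescribes three sessions a week. For CONC, "Time will start from 15 min and increase to achieve 40 min in week 4"; ECC is worded almost identically. The combined arm aims for 20 min of each mode, and its session length in week 1 is not given. The article does not say that session time is removed from the accelerometer record.

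**The concern.** Two separate problems follow from the stated timing.

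1. **There is no pre-intervention value.** A recording made in the first training week comes after allocation and while the allocated programme is running. It may already contain an early effect of the arm. Subtracting it, or entering it as the Pre level of the time factor, can then hide or create a difference between arms.
2. **The recording mixes two things.** Round-the-clock wear for seven days captures all three weekly sessions. The target is habitual activity, yet the record also holds supervised exercise whose length the protocol raises between the two recordings. A patient whose everyday activity did not change at all could show an increase.

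The trial has no untrained control. The Discussion section on control and blinding relies on within-group as well as between-group comparisons to judge effectiveness, so an artefact shared by all arms goes straight into the within-group result. Physical activity level is one of the outcomes named in the Aim section. A baseline missed before the first session cannot be recovered later by analysis.

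**Working it through.** **Schedule.** "The total duration of the proposed study is 14 weeks". Check: 12 training weeks + 1 testing week before + 1 after = 14. The stated total is reproduced, so a testing week exists on each side of training and could hold the recordings.

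**Placement of the two recordings.** Under the accelerometry section they fall in training weeks 1 and 12. Under Experimental approach and Implication for practice they would fall before week 1 and after week 12. Both cannot be followed.

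**Prescribed session time inside each seven-day window.**

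Inputs, all from Training protocols: 3 sessions per week; session length starting at 15 min; 40 min reached in week 4 and taken as held to week 12.

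Formula: minutes in window = sessions per week × minutes per session.

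| Arm | Week 1 | Week 12 | Change per week | Change per day |
|---|---|---|---|---|
| CONC and ECC, all week-1 sessions 15 min (assumption) | 3 × 15 = 45 | 3 × 40 = 120 | +75 | 75 / 7 = 10.7 |
| Combined, week-1 sessions 15 min in total (assumption) | 3 × 15 = 45 | 3 × 40 = 120 | +75 | 10.7 |
| Combined, week-1 sessions 15 + 15 min (assumption) | 3 × 30 = 90 | 3 × 40 = 120 | +30 | 30 / 7 = 4.3 |

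The text fixes only where session time starts. If sessions lengthen within week 1, the first window holds more than 45 min and the rise is below 75, so +75 is the upper end for CONC and ECC.

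**What this does to each comparison.**

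- ECC versus CONC: 75 − 75 = 0 min/week from scheduled time alone.
- Combined versus either single-mode arm: from 75 − 75 = 0 to 75 − 30 = 45 min/week (45 / 7 = 6.4 min/day), depending on the unstated split.
- Time effect and within-group change: +30 to +75 min/week of prescribed cycling, not zero in any arm under these assumptions.

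**After the change proposed below.** With both recordings in the testing weeks, prescribed session time is 0 min in each window and contributes 0 min to the change. The total stays at 14 weeks.

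**The case against.** The best case for the plan has several parts, and some of it stands.

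- **The question is comparative, and CONC and ECC share one schedule.** This stands for that contrast: equal scheduled time largely cancels in the group-by-time interaction. It does not protect the time effect or the within-group changes, which the authors also intend to interpret, and it does not settle the combined arm.
- **Prescribed minutes are not bias.** This stands. A wrist sensor may register cycling weakly, so the effect on step count may be small, and the effect on activity intensity or sedentary time is unknown. The article gives no habitual activity level to set the minutes against.
- **Session time may be cut out in data processing.** A journal article can leave that rule to the full protocol or analysis plan, so its absence is not held against this one. Cutting sessions out would still not turn week 1 into a pre-training baseline.
- **Only one of many outcomes is involved.** This stands. The sample size refers to muscle cross-sectional area and the walking test, and neither depends on accelerometry.
- **Testing weeks are not typical weeks either.** This is partly right: they contain exercise tests, and the biopsy subgroup must avoid exercise for 48 h beforehand. These features recur at both time points, and the subgroup is planned at ten patients in each arm.

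A reader might also infer three stronger points that the article does not support. Travel to sessions does not inflate the change, because both weeks contain three trips. Arm-specific soreness or fatigue in week 1 is possible, but nothing in the article gives it a size. Whether activity persists after supervised sessions stop is not a stated aim, so the lack of a later follow-up is not a fault here.

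**Conclusion.** The point holds for the physical activity outcome. The article states a timing for the accelerometer measure that contradicts its own Pre/Post design and its own description of when daily activity is assessed. Followed as written, it yields no pre-intervention value of habitual activity.

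The size is +75 min/week of prescribed cycling (about 11 min/day) in CONC and ECC, and +30 to +75 min/week in the combined arm. These figures assume that all week-1 sessions have the starting length and that 40 min is held to week 12. They are prescribed exposure, and the resulting bias in counts, steps or sedentary time cannot be calculated from the article.

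Within-group changes and the time effect are contaminated, and contrasts with the combined arm may be. It would go too far to say that session time biases the ECC versus CONC comparison, since the schedules match. The remaining risk there is that a baseline taken on treatment may already contain an early arm effect. No other outcome is affected.

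**What to change.** Make the accelerometry, Experimental approach and Implication for practice sections agree by moving the two seven-day wear periods into the testing weeks that already exist:

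- the first is completed before the first training session, and the second starts after the last session;
- hours spent at test visits are excluded from the derived outcomes.

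Where wear in a training week cannot be avoided for a patient, remove the logged session windows before deriving counts, steps and sedentary time, and do not label a week-1 recording as a pre-intervention baseline.

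The cost is small: the same devices, the same wear time and no extra weeks. The downside is that testing weeks are somewhat atypical because of the exercise tests and, in the biopsy subgroup, the 48 h without exercise. Excluding visit hours does not remove that 48 h effect, but it is similar at both time points and in all arms.
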